### Health Economic Evaluation

To evaluate the cost-effectiveness of the INTeRAcT program, a trial-based cost-utility analysis will compare the costs and effects of the intervention and control groups over a 9-month time horizon postbaseline. Additionally, a Markov model will be used to estimate cost-effectiveness over a lifetime horizon.

The health economic data, including costs and effects, will be collected using a combination of methods. Baseline data will be gathered at T0. The cost data will be collected during the 9-month follow-up period through self-completion questionnaires and diaries. The diaries will be completed during the first and the ninth period of this study, while a digital questionnaire will be sent via mail monthly during the intervening months. Resource use related to the intervention will be obtained directly from the rehabilitation center. The effects will be measured at 3 assessment time points: T0, T1, and T2, with additional data digitally surveyed each month during the 9 follow-up periods (Figures 1-3). To reduce missing or erroneous data, the questionnaires and diaries are reviewed monthly. In case of missing or unclear information, the participant will be contacted for clarification.

#### Data: Costs and Utilities

This evaluation will incorporate costs and effects during this trial and follow-up period, adopting both health care and societal perspectives. Both perspectives will include costs covering expenses borne by health insurance as well as patient copayments. The health care perspective will include all direct costs, both medical and nonmedical, while the societal perspective will encompass all costs, including direct medical and nonmedical costs as well as indirect costs.

The direct medical costs include all costs for treatment and follow-up from the health care perspective, and all out-of-pocket contributions by the participant. The following types of resource use will be collected: primary care visits, emergency visits, inpatient stays, outpatient services, medication, diagnostic tests, and medical or ADL aids.

Direct nonmedical costs include transportation and accommodation expenses, as well as home care assistance.

Indirect costs comprise productivity loss (eg, number of days away from work) and productivity losses due to informal caregiving. The productivity losses of the participants and informal caregivers will be valued using the human capital approach [134]

The effects will be expressed in Quality-Adjusted Life Years (QALYs). To calculate QALYs, health-related quality of life (QoL) scores are multiplied by the length of time spent in a particular health state. For example, 1 QALY represents 1 year of life in perfect health. Health-related QoL will be collected through the EQ-5D-5L questionnaire [113] and quantified in utilities derived from the national values of the EQ-5D-5L [135]. QALYs will be calculated using the area under the curve method.

To estimate the costs corresponding to the participants’ resource use, participants will be asked to provide invoices related to these expenses to ensure accurate cost reporting. Additionally, national tariffs will be used for valuation (NHIDI, BCFI, National feedback reports on hospitalizations, national cost per working hour, national cost for transportation, etc).

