### Sample Size Calculation

The power calculation was performed based on the primary research question: the evaluation of the short-term clinical effect of the INTeRAcT intervention versus usual care at home on independence in daily living, measured using the FIM/SCIM (see the Clinical Evaluation section). As no previous studies have assessed functional independence in both stroke and SCI participants in the chronic phase as a combined group, the calculation was based on a relevant improvement for this mixed population. A total sample size of 90 participants will provide 80% power to detect a 12% significant and relevant difference [93,94] in FIM/SCIM scores between the 2 groups, assuming an SD of 20% [95,96] and a 2-tailed *α* of 0.05. This corresponds to an effect size of 0.6, which is considered a “medium” effect. To account for an expected dropout of 10%, further, 100 participants will be recruited.

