### Randomization and Blinding

To ensure the integrity of this study, the following randomization procedures have been implemented. Participants (n=100) are randomly assigned to 1 of 2 groups: the intervention group, “INTeRAcT” (n=50), or the control group, “usual care” (n=50). To achieve a balanced distribution across conditions and prior rehabilitation technology experience, participants are stratified by condition (stroke or SCI) and prior technology experience. The latter refers to previous participation in outpatient rehabilitation involving advanced technological devices at a frequency of at least 1 to 2 sessions per week for a minimum duration of 3 months. Allocation concealment is ensured using preprepared randomization lists with a block size of 2. As participants enter this study, an independent team member responsible for randomization, who is not involved in participant contact or data collection, assigns each participant to the next concealed allocation. Recruiters and assessors have no access to the allocation lists and are unaware of the randomization sequence or block size. To ensure objectivity and minimize bias, outcome assessments are conducted by an assessor blinded to treatment allocation. Group assignment will be revealed to participants after the first measurement (T0). In exceptional cases, early disclosure may occur due to practical arrangements for participation in the 3-week intervention; however, the assessor will remain blinded. Participants are instructed not to disclose their allocation. Physiotherapists, participants after T0, and researchers involved in follow-up, process evaluation, and economic evaluation cannot be blinded.

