#### Data Analysis

First, a trial-based health economic evaluation will be conducted to assess the cost-effectiveness of the intensive, personalized rehabilitation program compared to usual care. Individual participant data from both the intervention and control group will be used to estimate the costs and health effects of the intensive personalized rehabilitation program compared to usual care from baseline up to 9 months of follow-up. The cost-effectiveness of the intervention will be expressed in incremental cost per QALY gained, calculated as the incremental cost-effectiveness ratio (ICER):

$$ICER=\frac{\left({\text{mean expected cost}}_{\text{intervention}}-{\text{mean expected cost}}_{\text{control}}\right)}{\left({\text{mean expected effect}}_{\text{intervention}}-{\text{mean expected effect}}_{\text{control}}\right)}=\frac{€}{\text{QALY}}$$

The robustness of the results will be evaluated through a deterministic and probabilistic sensitivity analysis of both costs and effects. A univariate deterministic sensitivity analysis will be conducted to assess the relative impact of individual cost components on the ICER. The results will be visually presented using tornado diagrams. A probabilistic sensitivity analysis will be performed using bootstrapping with replacement, with a minimum of 1000 iterations, to estimate the 2.5% and 97.5% percentiles of the ICER distribution. As all costs occur within a 1-year timeframe, no discounting will be applied. All bootstrapped ICERs will be visualized on a cost-effectiveness plane to assess the uncertainty surrounding the ICER and the probability that the intervention is cost-effective at various willingness-to-pay thresholds. To illustrate these probabilities of acceptable ICERs, a cost-effectiveness acceptability curve will be used. In addition, exploratory subgroup analyses will be considered based on pathology, type and severity of stroke and SCI, and total rehabilitation dose.

Given the extensive data collection in this trial, some missing data may occur; therefore, appropriate data imputation techniques will be applied [136]. The analysis will be conducted using R (R Foundation) software, following the Belgian guidelines for health economic evaluations [137], and will be reported according to the Consolidated Health Economic Evaluation Reporting Standards [138].

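### The cost-utility analysis names no adjustment for baseline EQ-5D-5L utility or the stratification factors, which costs precision in the QALY difference and lets chance baseline imbalance move the point ICER

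*Protocol article*

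**What the plan says.** Under Health Economic Evaluation, Data: Costs and Utilities, the article derives utilities from the EQ-5D-5L and states that "QALYs will be calculated using the area under the curve method". The Data Analysis part of the same section says that "Individual participant data from both the intervention and control group will be used to estimate the costs and health effects" from baseline to 9 months. It then gives the ICER as an explicit formula (difference in arm mean cost over difference in arm mean effect) with percentile limits from at least 1000 bootstrap resamples, a cost-effectiveness plane and an acceptability curve. No covariate, stratum or baseline term appears in that description.

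Other sections bear on this:
- Health Economic Evaluation: effects are measured at T0, T1 and T2, with further monthly surveys, so baseline utility is available.
- Randomization and Blinding: "participants are stratified by condition (stroke or SCI) and prior technology experience". Utility is not a stratification factor.
- Clinical Evaluation, Data Analysis: change from T0 is modelled with both stratification variables as fixed factors. The same approach is applied to the secondary outcomes, one of which is the EQ-5D-5L.

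**The concern.** A participant's utility at T0 predicts the later utilities that make up most of the area under the curve. If the arms differ at T0 by chance, most of that difference carries into the 9-month QALY difference unless the analysis conditions on it. The QALY difference is the denominator of the ICER and is likely to be small over 0.75 year, so a modest shift can move the point ICER and the acceptability curve noticeably.

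The same utility data would be baseline-referenced and stratum-adjusted as a clinical secondary outcome, yet enter the ICER as levels. Data Handling and Dissemination plans the combined clinical and economic results for one first paper, where the two could look inconsistent. The economic result is intended to inform reimbursement, so avoidable noise in it has a cost.

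**Working it through.** **The plan's own figure.** The only quantitative planning concerns the primary outcome: "A total sample size of 90 participants will provide 80% power to detect a 12% significant and relevant difference", "assuming an SD of 20% [95,96] and a 2-tailed" alpha of 0.05. The standardised effect is 12/20 = 0.6. The normal approximation gives 2 × (1.96 + 0.842)² / 0.6² = 43.6, so 44 per arm. The t-test version gives 44.6, so 45 per arm and 90 in total. Then 90/0.90 = 100. The stated figures are reproduced. The article gives no utility SD, correlation or expected QALY gain.

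**Inputs.** From the article: 50 per arm and a horizon of 9 months = 0.75 year. Assumed: utility SD 0.20 to 0.25 (wider range 0.20 to 0.30), baseline to follow-up correlation r = 0.7 (wider range 0.5 to 0.8), sustained utility gain 0.03 to 0.10.

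**Step 1: chance imbalance at T0.** SE = SD × √(2/50) = SD × 0.2, which is 0.040 at SD 0.20 and 0.050 at SD 0.25.

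**Step 2: carry-over into QALYs at a one-SE imbalance.** 0.75 × r × SE:
- SD 0.20: 0.75 × 0.7 × 0.040 = 0.021
- SD 0.25: 0.75 × 0.7 × 0.050 = 0.026 (95% range ±0.051)
- wider range: 0.015 (SD 0.20, r 0.5) to 0.036 (SD 0.30, r 0.8)

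**Step 3: compare with an assumed effect.** QALY gain = 0.75 × utility gain. The last two columns give the chance that the carry-over, in either direction, is at least as large as the effect.

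| Utility gain | QALY gain | SD 0.25, r 0.7 | Wider range |
|---|---|---|---|
| 0.03 | 0.0225 | 39% | 13–53% |
| 0.05 | 0.0375 | 15% | 1–30% |
| 0.08 | 0.060 | 2% | at most 10% |
| 0.10 | 0.075 | 0.4% | at most 4% |

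**Step 4: precision.** Treating the QALY as 0.75 × follow-up utility, at SD 0.25 the unadjusted SE is 0.75 × 0.050 = 0.0375. The adjusted SE is 0.0375 × √(1 − 0.7²) = 0.0268. The share of variance removed is r²: 49% at 0.7, 25% at 0.5 and 64% at 0.8.

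**Step 5: check by simulation.** The simulated curve used T0, 3 weeks and monthly points to month 9, with SD 0.25, equal correlation 0.7 between all visits, 50 per arm and no true effect. The SE fell from 0.0315 to 0.0176, so 1 − (0.0176/0.0315)² = 69% of the variance was removed. Both estimators averaged about zero. The SD of their difference was 0.026, matching step 2.

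**Where the carry-over comes from.** With the next measurement at 3 weeks, the trapezoid weight of T0 is 1.5/52 = 0.029 year, about 4% of 0.75. Almost all of the effect therefore acts through the correlation with later utilities.

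**The case against.** The strongest reply is that the article is silent and does not commit to a crude comparison. The area-under-the-curve sentence defines each participant's QALY, which is also the first step of an adjusted analysis. The ICER formula speaks of expected means, which could be model-based. The article cites Belgian guidelines, and a fuller economic plan may list covariates. This stands to a degree: a reader might infer that the plan declares raw differences, and it does not. But the estimator is described in detail, down to formula, resampling and displays, and no model is mentioned. Followed as written, it gives unadjusted means.

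A reader might also infer a biased ICER. That is not supported. Randomisation makes the unadjusted difference unbiased, and the bootstrap already includes chance baseline variation.

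A third tempting reading is that imbalance is as large as any plausible effect. The figures do not support that either. All effect sizes are assumed, a one-SE carry-over at r = 0.7 is below the 0.0375 QALY of a 0.05 gain, and for gains of 0.08 or more it rarely matters. Stratified blocks of two also nearly balance pathology and technology experience, so step 1 overstates the imbalance to the extent that these explain utility.

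Finally, the EQ-5D-5L will be reported relative to baseline among the clinical outcomes. That helps the reader but does not enter the ICER.

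**Conclusion.** The point holds as one of efficiency and pre-specification. The described analysis names no use of baseline utility or the strata, and adding them is a clear improvement at almost no cost. Under SD 0.20 to 0.25, r = 0.7 and 50 per arm, a one-SE imbalance shifts incremental QALYs by 0.021 to 0.026. That is comparable to the 0.0225 QALY of a sustained 0.03 gain and somewhat below the 0.0375 of a 0.05 gain. Adjustment removes about half of the variance in closed form, equivalent to a sample 1/(1 − 0.49) = 1.96 times as large for the QALY comparison; the simulated curve suggests more. SD, correlation and effect are all assumptions, and no systematic bias is claimed.

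Timing adds weight. The article says that researchers in the economic evaluation cannot be blinded, that data collection has ended and that analysis is ongoing. Adjustment chosen after the T0 imbalance is seen would be a discretionary choice.

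**What to change.** In the health economic analysis plan:
- Make the primary incremental QALY the arm coefficient from a regression of QALYs on arm, baseline EQ-5D-5L utility, pathology and technology experience.
- Refit it within each bootstrap draw, together with an incremental cost model adjusted for the same strata, so that the correlation between cost and effect is kept.
- Use these adjusted differences in the ICER, the cost-effectiveness plane and the acceptability curve.
- Report the unadjusted result as a sensitivity analysis.

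Baseline cost is not proposed as a covariate, because the article describes cost collection only during follow-up. Joint estimation such as seemingly unrelated regression is optional.

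The cost is a paragraph of plan wording and a few lines of R. Baseline utility is collected at T0 and both strata are known at randomisation, so no new data are needed. The choice should be fixed and dated before the arms are compared.

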#### Data Analysis

First, a trial-based health economic evaluation will be conducted to assess the cost-effectiveness of the intensive, personalized rehabilitation program compared to usual care. Individual participant data from both the intervention and control group will be used to estimate the costs and health effects of the intensive personalized rehabilitation program compared to usual care from baseline up to 9 months of follow-up. The cost-effectiveness of the intervention will be expressed in incremental cost per QALY gained, calculated as the incremental cost-effectiveness ratio (ICER):

$$ICER=\frac{\left({\text{mean expected cost}}_{\text{intervention}}-{\text{mean expected cost}}_{\text{control}}\right)}{\left({\text{mean expected effect}}_{\text{intervention}}-{\text{mean expected effect}}_{\text{control}}\right)}=\frac{€}{\text{QALY}}$$

The robustness of the results will be evaluated through a deterministic and probabilistic sensitivity analysis of both costs and effects. A univariate deterministic sensitivity analysis will be conducted to assess the relative impact of individual cost components on the ICER. The results will be visually presented using tornado diagrams. A probabilistic sensitivity analysis will be performed using bootstrapping with replacement, with a minimum of 1000 iterations, to estimate the 2.5% and 97.5% percentiles of the ICER distribution. As all costs occur within a 1-year timeframe, no discounting will be applied. All bootstrapped ICERs will be visualized on a cost-effectiveness plane to assess the uncertainty surrounding the ICER and the probability that the intervention is cost-effective at various willingness-to-pay thresholds. To illustrate these probabilities of acceptable ICERs, a cost-effectiveness acceptability curve will be used. In addition, exploratory subgroup analyses will be considered based on pathology, type and severity of stroke and SCI, and total rehabilitation dose.

Given the extensive data collection in this trial, some missing data may occur; therefore, appropriate data imputation techniques will be applied [136]. The analysis will be conducted using R (R Foundation) software, following the Belgian guidelines for health economic evaluations [137], and will be reported according to the Consolidated Health Economic Evaluation Reporting Standards [138].

Second, we will perform a model-based health economic evaluation. Conventional practice guidelines for cost-effectiveness analysis recommend using a time horizon that is sufficiently long to capture all relevant costs and outcomes, particularly for interventions targeting chronic conditions. In this case, a lifetime horizon as the base case analysis is often suggested [139,140]. As the absence of long-term follow-up data should not justify the failure to extend the time horizon to a relevant duration [140], a Markov model will be developed. This approach will allow us to account for the expected costs and health outcomes in both intervention and control groups beyond the follow-up period, to estimate the cost-effectiveness over a lifetime horizon. Estimates of resource use and utilities for each health state are derived from international peer-reviewed literature. Special attention will be given to the transferability of this data to the Flemish health care context, validated through monitoring within the research consortium. Discount rates of 3% for costs and 1.5% for utilities will be applied, following the Belgian guidelines [137]. In line with the trial-based evaluation, probabilistic sensitivity analyses will be conducted to account for uncertainty around the input parameters. R software to develop the model, calculate the incremental cost per QALY, and perform the probability sensitivity analysis.

Lastly, several scenario analyses will be conducted to simulate various implementation models of the intensive program compared to current usual care, such as providing 1‐2 intensive rehabilitation boosts per year, rather than dispersing the same therapy volume across an entire year (eg, 1‐2 h of therapy each week for a year).

A budget-impact analysis will also be performed to assess how the introduction of this intensive therapy might affect the care budgets. This analysis will consider (1) the annual incidence of the specific population for whom this therapy is suitable, (2) the number of centers required to provide this therapy, (3) the planning timescale, and (4) the total cost of expanding this therapy across Flanders.

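### Bootstrap percentiles of the ICER cannot be ordered or interpreted if a non-trivial share of replicates has a negative QALY difference; report intervals for net benefit, costs and QALYs instead

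*Protocol article*

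**What the plan says.** The Data Analysis text under Health Economic Evaluation defines the ICER as the difference in mean cost divided by the difference in mean effect, in euros per QALY, "over a 9-month time horizon postbaseline". On QALYs, the Costs and Utilities section states: "QALYs will be calculated using the area under the curve method". Uncertainty is to be assessed "using bootstrapping with replacement, with a minimum of 1000 iterations", in order "to estimate the 2.5% and 97.5% percentiles of the ICER distribution". The same paragraph adds two displays: "All bootstrapped ICERs will be visualized on a cost-effectiveness plane to assess the uncertainty surrounding the ICER", and, to show the probability of acceptable ICERs across willingness-to-pay thresholds, "a cost-effectiveness acceptability curve will be used".

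The text attaches no condition on the sign of the QALY difference to the percentile interval. It names no Fieller interval, and no interval for net benefit, incremental cost or incremental QALYs. The percentile pair is the only numerical interval that the article plans for this result.

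**The concern.** Percentiles presuppose that values can be ranked from better to worse. ICERs can be ranked that way only while the QALY difference keeps one sign. Once replicates fall on both sides of zero, two things go wrong:

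- Negative ICERs mix two opposite results: dominant (cheaper and better) and dominated (costlier and worse). Sorting places both at the low end, which reads as favourable.
- Close to a zero QALY difference the ratio runs off to plus or minus infinity, so the limits reflect small denominators and not the economics.

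A reader could take a negative lower limit as a cost saving when it comes from dominated replicates. This matters because cost-effectiveness is one of the stated hypotheses in the Introduction, and the evaluation is meant to inform reimbursement.

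**Working it through.** **The plan's own figures.** The article gives no ICER, QALY or cost value to reproduce. What it does give is the group size: 50 per arm, with 10% dropout allowed for, so 45 per arm evaluable. The sample size concerns FIM/SCIM and is consistent: 2 × (1.960 + 0.842)² × (20/12)² ≈ 43.6, so 44 per arm or 88 in total, against 90 stated; 90/0.90 = 100.

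**Step 1: can the QALY difference change sign?** For a true difference d and a QALY SD per person, SE = SD × √(2/n), and the share of negative replicates is about Φ(-d/SE). The values of d and SD are assumptions. With n = 50 per arm:

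| QALY SD | SE | d = 0.02 | d = 0.04 | d = 0.06 | d = 0.10 |
|---|---|---|---|---|---|
| 0.10 | 0.02 | 15.9% | 2.3% | 0.1% | <0.1% |
| 0.15 | 0.03 | 25.2% | 9.1% | 2.3% | <0.1% |
| 0.20 | 0.04 | 30.9% | 15.9% | 6.7% | 0.6% |

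With 45 per arm the shares are slightly higher (17% to 32% at d = 0.02). A sign change is plausible for small gains and negligible for large ones.

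**Step 2: what do the percentiles look like?** Independent normal draws of the two differences stand in for the bootstrap (2,000,000 draws). The assumed cost difference is EUR 6,000 (SE 2,500).

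| QALY difference (SE) | Dominated | Dominant | 2.5% and 97.5% of the ICER (EUR/QALY) |
|---|---|---|---|
| 0.03 (0.03) | 15.7% | 0.7% | about -1.8 million to +2.0 million |
| 0.05 (0.025) | 2.25% | 0.8% | about -22,400 to +754,000 |
| 0.10 (0.03) | 0.04% | 0.8% | about 10,400 to 172,000 |

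In the first row about 96% of the negative ICERs are dominated replicates. Ranked from better to worse, they would lie beyond the upper end; at 15.7%, well over 2.5%, no finite upper limit would exist. In the second row the lower limit is unstable at the planned minimum of 1000 iterations: over 2,000 simulated runs its 5th to 95th percentile range was about EUR -326,000 to +7,200, so its sign can depend on the random seed. In the third row the interval is orderly.

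**Step 3: the same replicates as net benefit.** For the first row, at an assumed EUR 50,000 per QALY:

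- Mean: 50,000 × 0.03 - 6,000 = -4,500.
- SE: √((50,000 × 0.03)² + 2,500²) = √(1,500² + 2,500²) ≈ 2,915.
- 95% interval: -4,500 ± 1.96 × 2,915, about EUR -10,200 to +1,200.
- Probability cost-effective: Φ(-4,500/2,915) ≈ 6%.

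This is well defined whatever the sign of the QALY difference.

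**Step 4: the acceptability curve.** If the curve were computed as the share of ICERs below EUR 50,000, the first row would give 22% instead of 6%, because dominated replicates have negative ICERs and would count as acceptable. The article does not say which computation is meant.

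**Step 5: coverage.** Simulated coverage of the percentile interval was about 95% to 98% with QALY differences of 0.02 to 0.05, SEs of 0.025 or 0.03 and the same cost inputs. In a wider grid it ranged from 87% to 98%; it fell to 87% to 90% only at a true QALY difference of 0.01 with a QALY SD of 0.15 to 0.20.

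**The case against.** The strongest reply is that the plan already covers decision uncertainty. The plane shows the quadrants, and the acceptability curve answers the reimbursement question at each threshold. Nobody need read the percentile pair alone, and a condensed article may leave net-benefit intervals to a fuller plan. Much of this stands: the two displays limit the harm, and the talk of plotting ICERs on the plane is loose wording, not an error. They do not repair the interval, however, and the interval is a stated method and not an omission.

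Four stronger readings are tempting, and the documents do not support them:

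- *The interval is bound to be meaningless.* That depends on a QALY difference and SD that the article does not give; at 0.10 (SE 0.03) the interval is usable.
- *It loses its 95% coverage.* The simulations do not show this as the general failure.
- *A negative lower limit always means dominated.* At 0.05 (SE 0.025) dominated replicates make up 2.25%, under the 2.5% cut. The limit is negative only because the 0.8% dominant replicates are sorted in with them.
- *The lifetime Markov model has the same defect.* The article plans probabilistic analyses there in line with the trial-based evaluation but specifies no ICER percentile interval.

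**Conclusion.** The point holds in conditional form. The planned percentile interval cannot be ordered or interpreted if a non-trivial share of replicates has a negative QALY difference. With about 50 per arm over 9 months that is plausible: 16% to 31% of replicates at a true difference of 0.02, 2% to 16% at 0.04, and at most 0.6% at 0.10, for assumed QALY SDs of 0.10 to 0.20. These figures rest on assumed QALY and cost inputs, normality, and independence of the cost and QALY differences. A prespecified interval should work across the plausible results, and this one does not. The damage is confined to one reported interval. The ICER point estimate, the plane, the primary clinical analysis and the sample size are unaffected.

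**What to change.** Replace the ICER percentile interval with the following, all from the same bootstrap:

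- the ICER as a point estimate;
- 95% bootstrap intervals for incremental cost, incremental QALYs and incremental net monetary benefit over a range of thresholds;
- the share of replicates in each quadrant.

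Give ICER percentiles only if essentially all replicates have a QALY difference of the same sign. Keep the cost-effectiveness plane. State that the acceptability curve is computed from net benefit and not from the share of ICERs below the threshold. Do the same in the model-based analysis if an ICER percentile interval would be reported there.

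The cost is a sentence or two in the plan and a few lines of R on replicates that will be generated anyway. No new data are needed, and the article reports that data analysis was still ongoing.
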